## Abstract

**Background & aims:**

Endoscopic ultrasound guided-biliary drainage (EUS-BD) is a promising alternative to endoscopic retrograde cholangiopancreatography (ERCP); however, its growth has been limited by a lack of multicenter randomized controlled trials (RCT) and dedicated devices. A dedicated EUS-BD lumen- apposing metal stent (LAMS) has recently been developed with the potential to greatly facilitate the technique and safety of the procedure. We aim to compare a first intent approach with EUS-guided choledochoduodenostomy with a dedicated biliary LAMS vs. standard ERCP in the management of malignant distal biliary obstruction.

**Methods:**

The ELEMENT trial is a multicenter single-blinded RCT involving 130 patients in nine Canadian centers. Patients with unresectable, locally advanced, or borderline resectable malignant distal biliary obstruction meeting the inclusion and exclusion criteria will be randomized to EUS-choledochoduodenostomy using a LAMS or ERCP with traditional metal stent insertion in a 1:1 proportion in blocks of four. Patients with hilar obstruction, resectable cancer, or benign disease are excluded. The primary endpoint is the rate of stent dysfunction needing re-intervention. Secondary outcomes include technical and clinical success, interruptions in chemotherapy, rate of surgical resection, time to stent dysfunction, and adverse events.

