### Endpoints

The primary endpoint is the rate of stent dysfunction (including both migration and occlusion) needing endoscopic or radiological re-intervention (Table 2). Patients who reach the primary endpoint are considered to have completed the study once hospitalization time for stent dysfunction and delays in chemotherapy treatment have been captured. Patients who do not reach the primary outcome are followed until surgery, death, or up to 1-year post stent insertion.

**Table 2 Tab2:** Criteria for primary endpoint of stent dysfunction

Meeting one or more of the following criteria:	
□ Suspected cholangitis [13]	
□ Definite cholangitis [13]	
□ 50% increase in bilirubin from the lowest level post index procedure	
□ 20% increase in bilirubin from the lowest level post index procedure AND evidence of obstruction on imaging (US/CT/MRI)	
AND:	
□ Endoscopic or radiological re-intervention confirming stent blockage or migration needing stent cleaning, stent change, and/or additional stent insertion

**Table 3 Tab3:** Secondary endpoints

1. Technical success defined as successful insertion of a transpapillary stent or choledochoduodenostomy stent at the initial procedure at time of randomization [6–8]	
2. Clinical success defined as 50% decrease in bilirubin < 2 weeks post-stent insertion or less than 25% of pre-procedure bilirubin level within 4 weeks post stent insertion [6]	
3. Stent patency defined as mean time to stent obstruction or migration (patient will be censored at last-follow-up or death)	
4. Proportion of patients with interruptions in chemotherapy treatment due to recurrent stent dysfunction	
5. Early adverse events (within 14 days of index procedure) as defined per the ASGE lexicon for endoscopic adverse events [18], including post-procedural pancreatitis, bleeding, intestinal perforation, and cholangitis	
6. Delayed adverse events (greater than 14 days of index procedure until last follow-up or death)	
7. Cost-effectiveness analysis	
Additional outcomes	
1. Median number of days in delayed chemotherapy treatment if interrupted	
2. Procedure time defined as from insertion of the endoscope to endoscope withdrawal1	
3. Fluoroscopy time	
4. Rate of hospitalization and length of stay	
5. Mortality	

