### Data collection

Collected data include primary, secondary (Table 3), and additional endpoints listed above, demographics, ASA score, Karnofsky index, type of sedation used, laboratory investigation including complete blood count, coagulation profile, liver enzymes, tumor staging based on the TNM classification for pancreatic cancer, quality of life data using the EQ-5D, peri-endoscopic data such as use of rectal indomethacin, antibiotics, and technical details including type of endoscope, EUS and ERCP accessories including stent type and size, sphincterotomy or tract dilation performed prior to stent insertion. Data are collected at the index procedure, and also at days 7, 30, 90, 180, 270, and 1 year post-randomization.

All data will be collected by research personnel who have been previously trained to use both the randomization website (randomize.net) and the data capturing software (redCAP). These research personnel are also GCP (Good Clinical Practices) and SOP (Standard Operating Procedures) certified. All data collected will be de-identified, meaning that information such as name, date of birth, hospital identifier, and Medicare number will not be stored in the main database. Each participant will be referred to by their study number. There will be a separate file stored in a password protected and encrypted computer with the decoder of identifiables in case these patients need to be contacted. All data will be stored for 7 years after publication or as requested in Standard Operating Procedure (SOP) from individual sites. Only data relevant to the study as outlined in this protocol will be collected by the research team. All information collected during the research project will remain confidential.

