##### Primary endpoint

Rate of re-intervention: Based on RCT data and retrospective series using LAMS [6–8, 10–12], we estimate a re-intervention rate of 30% vs. 10% for the ERCP and EUS-BD groups, respectively up to a 1-year follow-up period. To achieve a statistical power of 80% with a two-sided type I error of 5%, a total of 124 patients (62 in each arm) is required. Taking into account a 5% dropout rate, a final sample of 130 patients (65 patients in each arm) is needed.

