## Discussion

The ELEMENT trial is a multi-center randomized trial designed to address the question of whether EUS-BD with LAMS is associated with fewer episodes of stent dysfunction and need for re-intervention compared to standard ERCP in the management of malignant distal biliary obstruction. This clinical trial will also compare the technical and clinical success, adverse events, time to stent dysfunction, and oncological outcomes such as interruptions in chemotherapy, rate of surgical attempt, and survival.

We recently completed a meta-analysis of randomized controlled trials (RCT) comparing EUS-BD vs. ERCP or EUS-BD vs. radiological percutaneous biliary tube drain insertion (PTBD) [14]. Overall, we identified three trials comparing EUS-BD to ERCP [6–8]. Technical and clinical success was similar between modalities; however, rates of re-intervention favored EUS-BD over ERCP (RR 0.40; 95% CI 0.29–094) and PTBD (RR 0.49; 95% CI, 0.28–0.88). In addition, EUS-BD was comparable in terms of safety to ERCP while demonstrating lower rates of adverse events when compared to PTBD (RR 0.59; 95% CI, 0.39–0.87). Although results from this meta-analysis are promising, the studies were single-centered and small, using mostly non-EUS dedicated devices.

The potential for less stent dysfunction requiring reintervention with EUS-BD over ERCP, if shown in our proposed trial, would be of great clinical significance not only because of the diminished morbidity in this often-frail patient population, but also because of the potential impact on oncological outcomes. For patients with metastatic pancreatic cancer with a good performance status, there is a clear survival benefit attributable to FOLFIRINOX therapy [15], which would be necessarily delayed if reinterventions are needed. Furthermore, there has been a push to give neoadjuvant chemotherapy [16, 17] even in resectable disease, meaning that the insertion of a reliable biliary stent that remains patent for longer is likely to become a cornerstone for optimizing oncological outcomes. From a practical efficiency (and perhaps cost-effectiveness) perspective, EUS also has the unique ability to achieve decompression and acquire precise tissue diagnosis at the same clinical setting.

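### The surgical outcome is resection in the abstract, attempt in the Discussion and absent from Table 3, and follow-up stops at the primary event, so later surgery can be missed unequally between arms

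*Protocol article*

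**What the plan says.** The abstract (Methods) gives the secondary outcomes in one sentence: "Secondary outcomes include technical and clinical success, interruptions in chemotherapy, rate of surgical resection, time to stent dysfunction, and adverse events". The Discussion says the trial will also compare "oncological outcomes such as interruptions in chemotherapy, rate of surgical attempt, and survival".

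The Endpoints section prints the full list in Table 3. The secondary endpoints end at "7. Cost-effectiveness analysis", and five additional outcomes follow, ending with mortality. No entry in either part concerns surgery. The Data collection section then ties collection to that list: "Collected data include primary, secondary (Table 3), and additional endpoints listed above", followed by a list of baseline and procedural items with no entry for type or completion of surgery.

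Surgery appears in two other roles. The ERCP part of the Treatment protocol names it among the additional procedures that may follow the index procedure and will be recorded; the Follow-up section likewise says additional therapeutic approaches are recorded. The Endpoints section also uses it to end follow-up: "Patients who do not reach the primary outcome are followed until surgery, death, or up to 1-year post stent insertion". For everyone else, "Patients who reach the primary endpoint are considered to have completed the study" once the hospital stay and any chemotherapy delay have been captured; surgery is not among the items still to be captured. The Follow-up section repeats that follow-up ends at whichever of these events comes first.

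**The concern.** Resection and attempt are different outcomes. Where the population includes borderline resectable and locally advanced disease, and randomisation is stratified on resectability, some patients can be expected to go to theatre and not be resected. They count under one term and not the other. With neither term in the endpoint table, a reader of the eventual report cannot tell from this document which outcome was intended.

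The follow-up rule adds a second problem that a choice of term does not cure. Leaving the study at the primary event makes observation of later surgery depend on stent dysfunction, which is what the trial expects to differ between arms. A surgical rate with all randomised patients as denominator would then be under-counted more in the arm with more dysfunction, and the other arm would look better on surgery for that reason alone.

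**Working it through.** **Do the abstract's outcomes map to Table 3?**

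- Technical success: secondary endpoint 1.
- Clinical success: secondary endpoint 2.
- Time to stent dysfunction: secondary endpoint 3 (stent patency).
- Interruptions in chemotherapy: secondary endpoint 4.
- Adverse events: secondary endpoints 5 and 6.
- Surgical resection: no entry.

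The Discussion's survival corresponds to additional outcome 5 (mortality). Its surgical attempt has no entry. The surgical outcome is thus the only one named in either place that lacks an entry, and it is also the one whose name changes.

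**How is each kind of patient counted?**

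- Resected: event under both terms.
- Explored, not resected: event under attempt, non-event under resection.
- No operation: non-event under both.

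Only the middle group changes status. The documents give no rate for it. *For illustration only*, assume 20% to 40% of the 65 patients per arm go to surgery and 10% to 30% of those are not resected:

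- lowest: 65 × 0.20 × 0.10 = 1.3 patients per arm
- highest: 65 × 0.40 × 0.30 = 7.8 patients per arm

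This counts reclassified patients. It is not an estimate of bias, since such patients can occur in either arm.

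**The plan's own figure.** The sample-size section states: "we estimate a re-intervention rate of 30% vs. 10% for the ERCP and EUS-BD groups". With two-sided 5% error and 80% power, the pooled-variance formula without continuity correction is

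n = [1.960 × √(2 × 0.20 × 0.80) + 0.842 × √(0.30 × 0.70 + 0.10 × 0.90)]² / 0.20² = (1.109 + 0.461)² / 0.04 ≈ 61.6, so 62 per arm.

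That is the stated 62. Allowing 5% dropout, 124 / 0.95 = 130.5, against the stated 130, which is within rounding. The event rates used next are therefore the ones on which the trial was sized.

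**Who leaves at the primary event?** With 65 per arm:

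- ERCP: 65 × 0.30 = 19.5 patients
- EUS-BD: 65 × 0.10 = 6.5 patients
- difference: 13 patients, or 20 percentage points of each arm's denominator

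These are the patients whose later surgery the follow-up rule does not promise to observe. They are a ceiling on the number of operations lost.

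**From patients to operations.** Let *s* be the proportion of patients with a primary event who would have surgery afterwards and within the year. Operations missed per arm are 65 × (event rate) × *s*. If *s* is the same in both arms, the artificial difference in surgical rate is (0.30 − 0.10) × *s*. The documents do not give *s*. Borrowing the assumed 20% to 40%:

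- ERCP: 19.5 × 0.20 = 3.9 to 19.5 × 0.40 = 7.8 missed
- EUS-BD: 6.5 × 0.20 = 1.3 to 6.5 × 0.40 = 2.6 missed
- artificial difference: 0.20 × 0.20 = 4 to 0.20 × 0.40 = 8 percentage points, in favour of EUS-BD

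At *s* = 0 the effect vanishes, and *s* could be low if dysfunction occurs mostly in patients who are never surgical candidates. The direction follows from the plan's assumed rates; the size depends on *s*.

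**The case against.** The strongest reply is that this is a wording slip in a condensed article. The full protocol and the SAP are not shown, and either may define the surgical outcome before anyone sees the data. The analysis personnel are blinded, no conclusion in the article rests on the surgical rate, and the outcome is neither primary nor powered.

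Much of that stands, and it rules out several stronger readings.

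- A reader might infer that the definition will be chosen once results are known, or picked for its favourable answer. The document does not show that; it shows only that the choice is not made here.
- A reader might infer that surgery is recorded solely as a reason to stop follow-up. The Treatment protocol and Follow-up sections contradict this, since additional procedures, surgery included, are recorded. What is not stated is that resection will be told apart from exploration without resection.
- A reader might take "Only data relevant to the study as outlined in this protocol will be collected by the research team" as barring collection of surgical detail. The sentence sits in a paragraph on de-identification and confidentiality, and a surgical outcome is in fact named in the abstract and Discussion.
- A reader might infer that palliative bypass would be counted as an oncological gain. No section plans such an analysis.

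The reply does not remove the contradiction. The article prints a complete endpoint table that disagrees with its own abstract, and the abstract and Discussion name different outcomes. An SAP may refine a definition, but should not have to decide which of two outcomes the protocol meant. Nor does a definition supplied elsewhere change the follow-up rule printed here.

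**Conclusion.** The point holds as a contradiction within the document and a gap in observation. The surgical outcome has two names with different meanings and no entry in Table 3. Under either name, the printed follow-up rule makes no provision for surgery after a primary event, and at the planning rates that concerns about 20 of 65 ERCP patients against 6 to 7 of 65 EUS-BD patients.

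The imbalance rests on those planning rates being roughly right and on surgery after the primary event not being captured in some way the article omits. The counts of reclassified patients and missed operations rest wholly on assumed rates and should not be cited as findings. This should be corrected, but it does not threaten the trial's main result: the outcome is secondary and unpowered, and neither the primary endpoint nor the sample size depends on it.

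**What to change.** 1. Add one surgical outcome to Table 3: completed resection of the primary tumour within 1 year of randomisation, with all randomised patients as denominator.
2. Report surgical attempt without resection as a separate, separately named outcome.
3. Use the same terms in the abstract and the Discussion.
4. Record the type and date of surgery for every randomised patient to 1 year, including those who have already reached the primary endpoint, and say so in the Endpoints and Follow-up sections. Without this step, the outcome in step 1 would itself be observed unequally between arms.

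The cost is a table entry, one form field, matching wording, and limited chart review after the primary event. The Follow-up section already allows chart review for patients who cannot be reached, so the route exists. At the planning rates the extra review covers about 19.5 + 6.5 = 26 patients. The sample size and the primary analysis do not change.

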**Discussion:**

The ELEMENT trial is designed to assess whether EUS-guided choledochoduodenostomy using a dedicated LAMS is superior to conventional ERCP as a first-line endoscopic drainage approach in malignant distal biliary obstruction, which is an important and timely question that has not been addressed using an RCT study design.

**Trial registration:**

Registry name: ClinicalTrials.gov. Registration number: NCT03870386. Date of registration: 03/12/2019.

## Background

EUS-biliary drainage (BD) is a promising alternative to ERCP for the management of malignant distal biliary obstruction. Although ERCP has been the standard of care over the past four decades, the transpapillary route is associated with the risk of post-ERCP pancreatitis (PEP) while the insertion of a metal stent through the tumor can lead to subsequent stent dysfunction secondary to tumor tissue stent ingrowth and/or overgrowth in 20 to 40% of the patients [1–5]. EUS-BD through the transluminal approach is especially adapted to managing malignant distal biliary obstruction since a biliary bypass is created with a stent either through a choledochoduodenostomy (CDS) from the duodenal bulb or a hepatogastrostomy, thereby limiting the risk for PEP and stent tumor tissue ingrowth or overgrowth [6].

Recent small RCTs comparing EUS-BD with ERCP suggest similar technical success and safety profile while potentially being associated with lower rates of stent dysfunction [6–8]. Major limitations of trials having assessed this comparison to date are the small sample sizes with two of the three studies being underpowered in addition to being single center initiatives, thus limiting the generalizability of the findings. In addition, one of the major limiting factors for EUS-BD has been the lack of dedicated devices making the procedure technically complex [9]. Recently, a lumen-apposing metal stent (LAMS) has been developed specifically for EUS-BD that has been approved in Canada, Asia, and Western Europe (not yet FDA approved). Cohort studies have shown encouraging results [10–12]; however, prospective trials, let alone randomized trials, are lacking.

The role of EUS-BD using LAMS as a viable alternative to ERCP as the first-line modality in malignant distal biliary obstruction is a growing question, which has never been studied in a multicenter randomized controlled trial. Our pan-Canadian RCT thus assesses whether EUS-BD with a biliary LAMS is superior to ERCP.

## Methods

### Design and objectives

The Eus-guided biliary drainage with LumEn apposing Metal stENT vs. ercp (ELEMENT) trial is a multicenter prospective randomized controlled trial, across nine sites in Canada, comparing EUS-CDS with a biliary LAMS vs. ERCP in the initial endoscopic management of malignant distal biliary obstruction (Fig. 1). We hypothesize that EUS-CDS using LAMS is associated with fewer episodes of stent dysfunction and need for re-intervention when compared to standard ERCP while being comparable in safety and technical success in patients with malignant distal biliary obstruction (Additional file 1). At the time of writing this manuscript, this trial has been approved by the IRB of the coordinating center and two additional participating sites. All other sites have submitted their IRB application and will only start patient recruitment once approved.

**Fig. 1 Fig1:**
[figure not shown]
ERCP with traditional metal stent versus EUS-BD with LAMS

### Study population

Patients with malignant distal biliary obstruction meeting the criteria below (Table 1) will be considered for consent. All centers involved are busy tertiary care university-affiliated institutions that perform approximately 1000 ERCP and 1000 EUS per year.

**Table 1 Tab1:** Eligibility criteria

Inclusion criteria (must fulfill all)	
1. Radiological diagnosis (with or without pathological confirmation) of borderline resectable, locally advanced, or unresectable malignant distal biliary obstruction at least 2 cm distal to the hilum (resectability based on tumor staging on axial imaging and physician evaluation)	
2. Elevated liver tests with serum bilirubin at least three times above the upper limit of normal (1.2 mg/dl) Dilated extra-hepatic bile duct measuring at least 1.2 cm on axial imaging or US	
3. Karnofsky index > 30%	
4. ASA score < IV, and	
5. Provision of informed consent	
Exclusion criteria (any of the following)	
1. Hilar obstruction	
2. Uncorrectable coagulopathy and/or thrombocytopenia	
3. Age < 18	
4. Liver metastasis > 30% of the liver volume	
5. Liver cirrhosis with portal hypertension or ascites	
6. Prior biliary sphincterotomy or stent placement	
7. Surgically altered anatomy	
8. Patient with clinical and radiological evidence of gastric outlet obstruction	

### Patient identification and consent

Patients are identified by the treating team through referrals made to the participating physician or participating hospital center for drainage of biliary obstruction. Patients meeting the criteria above are approached by the treating endoscopist prior to the procedure. The endoscopist introduces the trial briefly to the patient to assess whether he or she would be interested in speaking to the research assistant. If agreeable, the patient is then approached by the research assistant who will perform the consent process including a detailed explanation of the trial such as risks, benefits, methods, and inconveniences to the participants. Patients are given a copy of the consent form and given the time to read the entire document and will be given the opportunity to ask any questions prior to consent. The patient is reminded that consent is completely voluntary and can be withdrawn at any time.

### Randomization

Patients included are randomized in a 1:1 ratio, in blocks of four, stratified by site and resectability: borderline resectable/locally advanced versus unresectable malignant distal biliary obstruction (Fig. 2 via secure Internet software (randomize.net)). Patients are randomized by a research assistant following consent. The endoscopist is then informed of the treatment allocation and the research nurse will verify that the correct assigned procedure is carried through and documented.

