**Fig. 2 Fig2:**
[figure not shown]
Enrollment, intervention, and assessment in the ELEMENT trial

The investigator’s research personnel are responsible for entering all criteria on randomize.net which will then generate the randomization sequence. The research personnel involved in the statistical analysis and patients, but not the endoscopists, are blinded to treatment allocation. To ensure the quality of the trial, unblinding will occur only in exceptional circumstances when knowledge of the treatment allocation is essential for the optimal management of the patient.

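### A single published block size of four within site and resectability lets an unblinded endoscopist who knows the earlier allocations predict a quarter to a third of the next ones

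*Protocol article*

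**What the plan says.** Four statements in the protocol article bear on this point.

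- **Block size and strata.** The Randomization section says: "Patients included are randomized in a 1:1 ratio, in blocks of four, stratified by site and resectability". Resectability has two levels, borderline resectable or locally advanced versus unresectable. The abstract repeats the single size: "in a 1:1 proportion in blocks of four". Nothing says that the size varies or is withheld from sites.
- **Who approaches patients.** Under Patient identification and consent: "Patients meeting the criteria above are approached by the treating endoscopist prior to the procedure". A research assistant then takes consent and randomises through a web system.
- **Who learns the allocation.** Under Randomization: "The endoscopist is then informed of the treatment allocation". The same section, after Fig. 2, says: "The research personnel involved in the statistical analysis and patients, but not the endoscopists, are blinded to treatment allocation".
- **Scale and stage.** The abstract describes a trial "involving 130 patients in nine Canadian centers". At the time of writing, the coordinating centre and two further sites had ethics approval. For the rest, Design and objectives says: "All other sites have submitted their IRB application and will only start patient recruitment once approved".

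**The concern.** In a block of four with two patients per arm, the fourth allocation always follows from the first three, and the third follows from the first two whenever those are alike. Central web randomisation after consent hides the list, but it does not stop inference from allocations already known.

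The exposed step is the one before consent: whether and when the endoscopist approaches an eligible patient. An operator who expects a particular arm next could, knowingly or not, hold back or bring forward a patient because of features visible before randomisation, such as imaging findings or expected difficulty of access. That would make the arms differ on prognosis for technical success, stent dysfunction and adverse events. The Analyses section plans chi-square and *t* tests, which do not adjust for such differences. Patients never approached are not in the data at all.

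**Working it through.** **Inputs from the protocol article.** 1:1 allocation; block size 4; 9 sites × 2 resectability levels = 18 strata; 130 patients. The article gives no predictability figure to reproduce. Its sample size enters only as the number spread over strata, and it does reproduce: n per arm = [1.96·√(2·0.2·0.8) + 0.8416·√(0.3·0.7 + 0.1·0.9)]² / 0.2² = (1.1087 + 0.4610)² / 0.04 = 61.6, so 62 per arm and 124 in total. The allowance for dropout takes this to 130. Then 130/18 ≈ 7.2 patients per stratum.

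**Step 1: one complete block, earlier allocations known.** There are six equally likely orders of AABB.

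| Position | Known with certainty | Best guess correct |
|---|---|---|
| 1 | 0 | 1/2 |
| 2 | 0 | 2/3 |
| 3 | 1/3 | 2/3 |
| 4 | 1 | 1 |
| Mean | (4/3)/4 = 33.3% | (17/6)/4 = 70.8% |

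**Step 2: incomplete last blocks.** With 7 patients in a stratum (one full block plus three positions):

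- certain: (4/3 + 1/3)/7 = 1.667/7 = 23.8%
- best guess correct: (17/6 + 11/6)/7 = 4.667/7 = 66.7%

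Spreading 130 as evenly as possible gives 14 strata of 7 and 4 of 8. Certain allocations: 14 × 1.667 + 4 × 2.667 = 34 of 130 = 26%; best guess 68%. Simulation with random stratum sizes (unresectable share 30–70%, equal or unequal site accrual, all assumed) gives about 28% certain (about 36 of 130) and 68%.

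**Step 3: several endoscopists who do not share.** Assume *k* endoscopists at a site take patients equally, and each knows the position in the block but only his or her own earlier allocations.

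- Position 3 is certain if both earlier patients were one's own and alike: (1/k²)(1/3).
- Position 4 is certain if all three earlier patients were one's own, or exactly two were and were alike: 1/k³ + 3(1/k²)(1 − 1/k)(1/3) = 1/k².

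The certain share is therefore the *k* = 1 figure divided by k².

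| k | 7 per stratum | 130 over 18 strata | Complete blocks | Best guess (130 over 18) |
|---|---|---|---|---|
| 1, or full sharing | 23.8% | 26.2% | 33.3% | 68% |
| 2 | 6.0% | 6.5% | 8.3% | 59% |
| 3 | 2.6% | 2.9% | 3.7% | 56% |
| 4 | 1.5% | 1.6% | 2.1% | 55% |

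**Step 4: tracking by site only.** An operator who knows all earlier allocations at the site but ignores resectability guesses right about 63% of the time (simulation).

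**Step 5: random blocks of 4 and 6.** Sizes are drawn with equal probability. The operator knows the set of sizes and all earlier allocations in the stratum, but not the sizes drawn. Exact enumeration gives 6.4% certain at 7 per stratum and 5.9% at 8, about 8 of 130 overall. The best guess is right 65.7% and 66.8% of the time.

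**The case against.** The strongest objection is that the high figures rest on a premise the article does not state. A reader might infer that each endoscopist learns every allocation at the site. The text says only that the endoscopist is told the allocation after a patient is randomised, which in context means that patient. Study population describes busy centres, each with about 1000 ERCP and 1000 EUS procedures a year, and more than one operator per site is plausible. Without sharing, certainty largely disappears (step 3). Prediction also has to be tracked by resectability as well as by site. This objection stands, and it is why the figures must be read as conditional.

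A reader might also picture an operator avoiding patients with a poor EUS window. The EUS-BD section has biliary access confirmed by EUS during the assigned procedure, after randomisation, and lack of a safe window counts as a technical failure. The eligibility criteria already exclude altered anatomy and gastric outlet obstruction and require a dilated duct. Selection on the window itself is therefore not supported; selection on imaging or expected difficulty remains possible.

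The safeguards count for something. A research assistant consents and randomises centrally, and the article gives the endoscopist no stated discretion to pass over an eligible patient. But the endoscopist still makes the first approach, and those safeguards do not block inference from past allocations.

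**Conclusion.** The point holds as a design risk. A single published block size, an unblinded operator and that operator's role in approaching patients are all stated. The size is about 24–33% of allocations certain and 67–71% guessable if the operator knows all earlier allocations in the stratum. With two operators who do not share, about 6–8% are certain, and fewer with more operators. Which case applies depends on the number of endoscopists per site and on how far they share allocations, neither of which is given.

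The documents do not support the stronger conclusion that selection has occurred or that the primary comparison is biased. The effect on 30% versus 10% has not been estimated, and the sample size is unaffected. The change is still worth making, because it is cheap and most sites were not yet approved at the time of writing.

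**What to change.** Replace the fixed size with randomly varying block sizes, for example 4 and 6, and do not disclose the sizes to sites. Apply this from the start at sites not yet open (nine minus the three approved at the time of writing leaves six) and from the next new block at open sites.

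The gain is mainly the removal of certainty: from about 24–33% of allocations to about 6%, even if the set of sizes becomes known. Best-guess accuracy falls only from about 67–71% to about 66–67%, so the change reduces the risk without removing it.

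The cost is a new list in the existing randomisation software, a short amendment, and slightly larger possible imbalance in small strata.
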